SI are temporarily relieved and stabilized through acute cannabis use (i.e., negative reinforcement).

*Hypothesis 1.1:* Negative mood will predict subsequent same-day cannabis use events as well as greater self-reported motivation to use cannabis for mood improvement (EMA Phase 1; Baseline as Usual).

*Hypothesis 1.2:* Negative mood and SI reported within one hour following cannabis use will be lower in intensity and less variable than mood and SI reported during same-day random-prompt EMA reports occurring ≥1 hours since last cannabis use (EMA Phase 1; Baseline as Usual).

*Hypothesis 1.3 (exploratory):* There will be within-subject correlates (e.g., concurrent other substance use, social context of use) and between-subject factors (e.g., cannabis use and depression severity, history of suicidal behavior) that moderate relationships between acute cannabis use and mood and SI.

**Aim 2:** To test if negative mood and SI decrease in overall (mean) levels and variability after cannabis

wash-out.

*Hypothesis 2.1:* Among CB-Abst but not CB-Mon, negative mood and SI reported during random prompt EMA reports will intensify and become more variable throughout the first week of sustained cannabis withdrawal (EMA Phase 2; Randomized Withdrawal) compared to random, non-use events during baseline cannabis use as usual (EMA Phase 1; Baseline as Usual).

*Hypothesis 2.2:* Negative mood and SI reported during EMA random prompts after 8 weeks of abstinence (EMA Phase 3; Randomized Sustained Abstinence) will be lower in intensity and variability than negative mood and SI reported during EMA random prompts occurring during random, non-use events during baseline cannabis use as usual (EMA Phase 1; Baseline as Usual) and withdrawal (EMA phase 2; Randomized Withdrawal). There will be no difference in mood or SI intensity or variability across the 3 EMA phases in CB-Mon.

1. **General Description of Study Design**

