**Data analysis.**

**Aim 1: To test if negative mood and SI are temporarily relieved and stabilized through acute cannabis use (i.e., negative reinforcement cycle).** We will only use phase 1 data, the 2-week baseline period in which all participants may use cannabis. *Hypothesis 1.1:* We hypothesize that negative affect measures for a) the current random prompt, and b) the prior random prompt (a lag-1 term) will predict 1) greater cannabis use independent of motivating reason (i.e., lower probability for the zero component of the model), and 2) higher scores for motivated cannabis use to improve negative mood. Negative affect measures will therefore be converted to z-scores for this analysis and included as predictors for both the zero and non-zero components of the model. *Hypothesis 1.2:* We hypothesize that the binary indicator for cannabis use in the last hour will predict lower, less variable scores for the negative affect measures. Therefore, the binary use indicator will be included as a predictor for the beta regression residual variance term as well. *Hypothesis 1.3 (exploratory):* There will be within-subject correlates (e.g., concurrent other substance use, social context of use) and between-subject factors (e.g., cannabis use and depression severity, history of suicidal behavior) that moderate relationships between acute cannabis use and negative affect.

**Aim 2: To test if negative mood and SI initially increase with the start of abstinence and then decrease in both mean levels and variability after cannabis wash-out.** We will use phase 1 – 3 data, including predictors for a) group differences (CB-Abst vs. CB-Mon), b) differences by phase (phase 3 vs. phase 1 and phase 2 vs. phase 1), and c) terms for the group by phase interactions. All terms will be included as predictors for the beta regression residual variance term as well. We will only include data for the CB-Abst group with confirmed abstinence for phases 2 – 3. *Hypothesis 2.1:* We hypothesize that CB-Abst will show higher mean negative affect scores and greater variability during phase 2 compared to phase 1, while CB-Mon will show no differences between phases. *Hypothesis 2.2:* We hypothesize that CB-Abst will show lower mean negative affect scores and less variability during phase 3 compared to phase 1, while CB-Mon will show no differences between phases.

**Exploratory analyses:** To further assess heterogeneity in suicidal ideation, we will conduct a set of

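### Hypotheses 2.1 and 2.2 compare with non-use prompts in phase 1, but the Aim 2 model neither restricts to such prompts nor adjusts for acute use

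*Protocol*

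**What the plan says.** Under Specific Aims and Objectives, Hypothesis 2.1 sets random prompts in the first week of withdrawal "compared to random, non-use events during baseline cannabis use as usual". Hypothesis 2.2 sets week 8 of abstinence against prompts "occurring during random, non-use events during baseline cannabis use as usual" and also against the withdrawal week. Both therefore have a non-use baseline, and Hypothesis 2.2 has two comparators.

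Under Statistical Analysis, Data analysis, Aim 2 is modelled on phase 1–3 data with a group term, "b) differences by phase (phase 3 vs. phase 1 and phase 2 vs. phase 1), and c) terms for the group by phase interactions". The same terms enter the residual-variance part. The one data filter is: "We will only include data for the CB-Abst group with confirmed abstinence for phases 2 – 3". Nothing is said there about prompt type in phase 1 or in CB-Mon. Hypothesis 2.1 is restated as "CB-Abst will show higher mean negative affect scores and greater variability during phase 2 compared to phase 1", without the non-use condition. Hypothesis 2.2 is restated against phase 1 only.

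Data preparation defines acute use as a yes/no indicator at each random prompt, covering the preceding hour. Hypothesis 1.2 uses that indicator and expects lower, less variable negative affect after use. Aim 2 does not mention it.

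**The concern.** Random prompts include prompts answered soon after use: the indicator is defined on them, and the General Description of Study Design says that prompts will capture mood during or shortly after use. A phase 1 mean over all prompts is therefore a mixture of use and non-use states, whereas abstinent CB-Abst contributes only non-use prompts in phases 2 and 3. A rise from phase 1 to phase 2 could then reflect loss of acute relief rather than withdrawal.

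Separating those two is the purpose of having Aim 1 and Aim 2, and Aim 2 is the trial's only randomized comparison. CB-Mon does not cancel the effect, because it keeps its use prompts throughout.

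**Working it through.** **Inputs from the protocol.** 7–9 prompts a day; phases of 14, 7 and 7 days; N = 200, ICC 0.09, d = 0.2, and 224 entries with 99% power for Hypotheses 2.1–2.2 (power table); use on at least 4 days a week (inclusion) and not more than 4 times a day (exclusion); time-of-day bins from 6:00 to 21:00, i.e. 15 h; a 1 h use window; pilot effect sizes 0.19 to 0.44.

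**Assumptions.** Prompts are spread evenly over the 15 h; all use falls in those hours with no overlapping windows; the pilot range stands in for the acute effect; two-sided alpha is 0.05; CB-Mon use is stable across phases.

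**Step 1: which prompts the power table counts.** At 8 prompts a day, 8 × (14 + 7 + 7) = 224. Effective N = 200 × 224 / (1 + 223 × 0.09) = 44,800 / 21.07 = 2,126, which gives 99.6% power for d = 0.2. The stated 99% is reproduced. The planning count has no prompts removed for use.

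**Step 2: what the contrasts estimate.** Let μ be the non-use mean, δ the fall after use and f the share of post-use prompts. Suppose abstinence does nothing except remove post-use prompts.

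| | Phase 1 | Phase 2 | Phase 3 |
|---|---|---|---|
| CB-Abst, abstinent | μ − fδ | μ | μ |
| CB-Mon | μ − fδ | μ − fδ | μ − fδ |

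In CB-Abst both contrasts against phase 1 equal +fδ. In CB-Mon both are 0. Both interactions are therefore +fδ. Phase 3 minus phase 2 is 0 in each arm, so that contrast does not carry the shift.

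**Step 3: size.** f = uses per day × 1 h / 15 h. The lower end takes one use on each of 4 days a week: 4/7 = 0.57 a day.

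| Uses/day | f | fδ, δ = 0.19 | fδ, δ = 0.44 | Share of d = 0.2 |
|---|---|---|---|---|
| 0.57 | 3.8% | 0.007 | 0.017 | 4–8% |
| 1 | 6.7% | 0.013 | 0.029 | 6–15% |
| 2 | 13.3% | 0.025 | 0.059 | 13–29% |
| 4 | 26.7% | 0.051 | 0.117 | 25–59% |

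**Step 4: effect on the test.** The phase 2 versus phase 1 interaction was simulated on a linear scale with 77 per arm and 85 and 43 prompts in the two phases, with abstinence having no effect of its own. The rejection rate at a nominal 5% was 6% to 97% over f = 0.04 to 0.27 when all persons shared the same phase change, and 5% to 53% when person-specific change had SD 0.3. At f = 0.13 the two ranges were 13–46% and 7–18%. With non-use prompts only, the mean spurious effect lay between −0.002 and 0.001, with rejection at about 5–6%.

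**Step 5: variability.** Mixing two states adds variance f(1 − f)δ², at most 0.267 × 0.733 × 0.44² = 0.038 SD². If post-use prompts are themselves less variable, that pulls the other way. In the top corner the two balance when post-use variance is (1 − f)δ² = 0.733 × 0.194 = 14% below non-use variance. The sign for variability is therefore open.

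**The case against.** The Aim 2 text names phases, not prompt types. The hypotheses already state the non-use reference, and the Statistical models paragraph allows further predictors as needed, so the protocol could be read as compatible with a non-use analysis. A reader might instead infer that the sponsor has decided to pool all prompts. The text does not say so outright, and the power table is only a planning count. What stands against the lenient reading is that the Aim 2 text lists its terms and its one filter, names the use indicator for Hypothesis 1.2 and leaves it out here, and restates the hypotheses without the non-use condition.

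The size is soft, and that stands. The pilot effects are not said to be acute-use effects and cover significant effects only. The top of the range puts every participant at the eligibility cap. The shift exists only if Hypothesis 1.2 is true. The product fδ is a linear-scale identity, whereas the planned model is a zero-inflated beta regression with a lag-1 term.

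Simply deleting post-use prompts is also open to objection: it breaks the lag-1 series and selects CB-Mon data on behaviour after randomization, which Hypothesis 1.1 links to mood. That is a reason to model use instead.

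**Conclusion.** The contradiction is within the protocol and does not depend on an unseen analysis plan: the stated hypotheses and the stated model have different baselines. Followed as written, and if acute use lowers negative affect, both contrasts against phase 1 and their interactions with group move upward by about 0.007 to 0.12 SD under the assumptions above.

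Four stronger readings are not supported:

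- The bias does not change sign between the hypotheses. It is upward in both contrasts, helping Hypothesis 2.1 and making Hypothesis 2.2 harder to show.
- The same direction cannot be claimed for variability.
- A false finding of withdrawal is not assured. The high rejection rates come from corner cases, and for light users the shift is negligible.
- The phase 3 versus phase 2 comparison is not beyond the model. It is a linear combination of fitted terms and is only missing from the listed contrasts.

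**What to change.** Keep all prompts. Add the use-in-last-hour indicator to the mean, residual-variance and zero parts of the Aim 2 model, and take the group-by-phase contrasts at no use. Report the all-prompt contrast as a sensitivity analysis. Restate the non-use condition in the Aim 2 text so that it agrees with Specific Aims and Objectives.

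Alternatively, if the all-prompt effect is what the sponsor wants, reword Hypotheses 2.1 and 2.2 accordingly and do not attribute a phase 2 rise to withdrawal alone.

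In either case, list the phase 3 versus phase 2 group-by-phase contrast under Hypothesis 2.2.

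The cost is a few extra parameters and slightly less precision; no new data are needed. Adjustment conditions on use after randomization in CB-Mon, and the interpretation should say so.

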**Treatment Assignment and/or Randomization**

If participants meet eligibility criteria and a signed consent form has been received from a parent/guardian, they may be contacted and scheduled for a baseline session. For participants aged 18 years, baseline sessions may be scheduled prior to obtaining consent (as consent will be obtained at baseline prior to administering any study procedures). For all participants, a member of the study team will discuss the consent/assent form with the participant, provide answers to any questions, and, if the participant is interested, a licensed clinician will obtain informed consent/assent. The participant will then be given a signed copy of the consent/assent form.

Once enrolled and after the baseline phase (EMA Phase 1; Baseline as Usual), participants will be scheduled for randomization, which will employ a 2-arm, within-subject, parallel group design to examine effects of short- and longer-term withdrawal across 8 weeks of cannabis abstinence on depression and SI. Participants will be randomized to 8 weeks of abstinence with contingency management (CB-Abst: n=100) or non-contingent monitoring with no abstinence requirement (CB-Mon: n=100) using a 1:1 ratio in blocks of 6. A subset of study staff who will administer surveys and questionnaires querying about mood and suicidality will be blind to group assignment. Randomization will be based on a computerized scheme developed by the study statistician. Randomization will be stratified by age (<=14 years old vs >=15 years old), sex (male vs female), and depression severity (mild/moderate vs. Moderately severe/severe). A key aspect of the approach is that the 8-week period is long enough to observe true changes due to cannabis discontinuation, separate from effects of cannabis withdrawal and residual cannabinoid exposure. Groups will complete 1-week of EMA in weeks 1 (EMA Phase 2; Randomized Withdrawal) and 8 (EMA Phase 3; Randomized Sustained Abstinence) of the randomized study period.

Individuals randomized to monitoring who incidentally stop using cannabis, or express an interest in discontinuing cannabis, will not be removed from the study. If desired, these individuals will be provided with substance use resources at the time of interest in cessation.

1. **STUDY PROCEDURES**

Study procedures are nearly identical to those used in IRB approved pilot protocol (#2021P002416).

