**Statistical models.** Separate analyses will be conducted for each negative affect measure. Statistical models will assume that a) data are a mixture of a non-zero continuous component and zeros, and b) the continuous component will follow a beta distribution (i.e., scores will be scaled to be between 0 and 1). Models will include 1) a participant-varying lag-1 autocorrelation term (to handle repeated measures) and 2) a participant-varying probability term governing the occurrence of zeros (to allow for individual differences). Additional covariates will include weekday (categorical, Monday-Sunday), time of day (categorical, 6:00-11:00, 11:00-16:00, 16:00-21:00), age (continuous), and gender (categorical). To test specific hypotheses, additional predictors will be included as needed for a) the beta regression, b) the residual variance term of the beta regression, and c) the probability term governing zeros.

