**Protocol non-adherence.** Analyses involving phase 1 and/or phase 2 of EMA data collection, will only consider CB-Abst participants who have biochemically-validated CB abstinence for two months because the goal is to study the effect of abstinence on change in mood and SI. If fewer than expected CB-Abst abstain from CB use for the full two months, we will form Helmert contrasts: those in CB-Mon (a), CB-Abst who do not abstain (b), and CB-Abst who abstain (c). The 1^st^ Helmert contrast will compare a to b+c and will be the intent to treat comparison. The 2^nd^ contrast will compare b to c, which corresponds to the post hoc sensitivity analysis of interest. Similar considerations will be made if participants in CB-Mon incidentally discontinue CB use during the study.

**Power analysis and justification of recruitment targets for the confirmatory cohort.** The R package ‘EMAtools’ (version 0.1.3; Kleiman, 2017) was used to determine the power for the proposed analyses. Preliminary analyses from the exploratory study found effect size estimates for significant effects ranged from 0.19 to 0.44, and that 77% of participants completed all phases of the study, completing on average 76% of all prompts. Estimates of the power were therefore computed to detect a weak effect (a Cohen’s d of .2) based on linear multi-level models using the nesting structure for the proposed EMA analyses and an intra-class correlation of .09. Table 1 shows the breakdown of estimates power based on the hypothesis being tested under two scenarios: 1) an ideal scenario with the full proposed number of participants and responses, and 2) a realistic scenario where 77% of participants complete 76% of entries.

Table 1: Power estimates by hypothesis and attrition scenario (ideal versus worse-case)

| Hypothesis | N (%) for sample size | N (%) of completed entries | Power |
| --- | --- | --- | --- |
| 1.1 - 1.2 | 200 (100%) | 112 (100%) | 99% |
|  | 154 (77%) | 85 (76%) | 93% |
| 2.1 - 2.2 | 200 (100%) | 224 (100%) | 99% |
|  | 154 (77%) | 170 (76%) | 94% |

1. **Monitoring and Quality Assurance**

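### The variability tests in H1.2, H2.1 and H2.2 make no stated allowance for adolescents who differ in lability, so they are too liberal if such differences exist

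*Protocol*

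**What the plan says.** The Statistical models paragraph of the Statistical Analysis section specifies a mixture of zeros and a beta-distributed non-zero part. It names two components that vary by participant: "a participant-varying lag-1 autocorrelation term (to handle repeated measures") and "a participant-varying probability term governing the occurrence of zeros (to allow for individual differences"). It then allows hypothesis-specific predictors to be added where needed to three parts of the model, one of which is "the residual variance term of the beta regression".

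The Data analysis paragraphs say what enters that term. For H1.2, "the binary use indicator will be included as a predictor for the beta regression residual variance term as well". For H2.1 and H2.2 the predictors are group, phase and group by phase: "All terms will be included as predictors for the beta regression residual variance term as well". These coefficients carry the variability half of the three hypotheses. No participant-varying part of this term, clustered standard error or other allowance for personal differences in spread is named. None is expressly ruled out either.

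**The concern.** Randomisation is by participant, while each participant is planned to answer up to 112 prompts in phase 1 and 224 over all phases. If some adolescents are habitually more labile than others, the prompts of one person are not independent evidence about variability. The lag-1 term handles serial dependence in the level of the scores. It does not handle stable or changing personal differences in their spread. A model with one shared precision then understates the standard error of a precision contrast.

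Differences in lability are plausible here: ages run from 12 to 18, any PHQ-9 score of 5 or more qualifies, and H1.3 itself expects between-subject moderators. At stake are claims that cannabis use stabilises mood and suicidal ideation, or that abstinence first destabilises and later stabilises them. The false-discovery-rate adjustment does not help, because it takes the p-values as valid.

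**Working it through.** **1. The plan's own figure.** Table 1 assumes d = 0.2 and an intra-class correlation of 0.09. Take effective N = participants × completed prompts / [1 + (full prompts − 1) × 0.09], split it into two halves, and set two-sided alpha at 0.05 (assumed; not stated). Power is Φ(0.2 × √(n per half / 2) − 1.96).

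- Aim 1, ideal: 200 × 112 / 10.99 = 2038, power 99.5% (stated 99%).
- Aim 1, realistic: 154 × 85 / 10.99 = 1191, power 93.2% (stated 93%).
- Aim 2, ideal: 200 × 224 / 21.07 = 2126, power 99.6% (stated 99%).
- Aim 2, realistic: 154 × 170 / 21.07 = 1243, power 94.1% (stated 94%).

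The table reproduces. It rests on linear multi-level models and does not address the variability tests.

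**2. The model as written and its alternative.** With mean μ and precision φ, the variance of a non-zero score is μ(1 − μ)/(1 + φ).

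- As written: log φ = γ0 + γ1x, with x the use indicator or the group and phase terms.
- With personal differences: log φ = γ0 + u + (γ1 + v)x, where u is a participant's level of log precision and v a participant's own change.

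The protocol gives neither SD(u) nor SD(v), so both are assumed. To show what they mean, take a central φ of 5. At SD(u) = 0.5, participants one SD above and below have φ = 5e^0.5 = 8.24 and 5e^−0.5 = 3.03, so their within-person SDs differ by √(9.24/4.03) = 1.51 times. At SD(u) = 0.3 the factor is √(7.75/4.70) = 1.28.

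**3. False-positive rates with no true variability effect.** Realistic scenario: 154 / 2 = 77 per arm, 85 phase-1 and 43 phase-2 prompts. Assumed: share of prompts with recent use Beta(2, 8), participant means known, no zeros, no autocorrelation. There were 600 runs per row, or 3000 for the rows marked *. Nominal rate 5%.

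| SD(u) | SD(v) | H1.2 use | CB-Abst, phase 2 vs 1 | Group × phase |
|---|---|---|---|---|
| 0 | 0 | 4-6% | 4-6% | 4-6% |
| 0.3 | 0 | 11% | 6% | 8% |
| 0.5* | 0 | 24% | 9% | 8% |
| 0.8 | 0 | 42% | 15% | 14% |
| 0.5 | 0.2 | 31% | 20% | 20% |
| 0.5* | 0.3 | 34% | 31% | 32% |
| 0.5 | 0.5 | 42% | 49% | 51% |

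The ideal scenario (100 per arm, 112 and 56 prompts) gives similar or slightly higher rates.

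**4. Other assumptions.**

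- With use probability logistic(N(−2.2, 0.8)) and SD(u) = 0.5, H1.2 is 24%. The two group-by-phase terms are 8-10%, rising to 34-35% with SD(v) = 0.25.
- A further set of runs gives 9% and 18% for H1.2 at SD(u) = 0.3 and 0.5. Aim 2 is about 6-11% with stable differences and about 23-25% with SD(v) = 0.25.
- With prompts thinned to 20% non-zero (assumed; 300 runs, error about 2 points), SD(u) = 0.5 and SD(v) = 0, H1.2 is 11% against 22% unthinned and Aim 2 is 9% against 12%. With SD(v) = 0.25 both are about 20-22%.

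**5. Why H1.2 and Aim 2 differ.** In Aim 2 each participant contributes to every phase in similar proportions, so a stable u largely cancels. In H1.2 it does not. Eligible use runs from 4 days a week (at one use per such day, 4/7 = 0.57 a day) to 4 times a day, a sevenfold range. The use indicator is therefore partly a between-person variable.

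**6. Does the remedy work?** Participant-clustered inference in the step 3 set-up gives 5.5-6.5% (H1.2), 5.7-6.0% (CB-Abst phase contrast) and 5.2-6.0% (group × phase) in the two 3000-run settings. In the set-up of the first bullet in step 4, clustering leaves H1.2 at 7-21% when heterogeneity is present, while Aim 2 comes down to about 5-8%. For the CB-Abst phase contrast with SD(u) = 0.5 and SD(v) = 0.3, a participant-varying intercept alone leaves about 25%. Adding the participant-varying change gives about 8% (96 runs each; error on the latter about 3 points).

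**The case against.** The strongest reply is that the protocol is silent rather than wrong. It does not say that the residual-variance predictors are the only content of that term, it fixes no standard-error method, and an SAP that is not at hand could add a participant-varying part. It is right that the protocol does not exclude one. But this is more than missing detail: the text lists which components vary by participant, and says that the zero-probability term does so to allow for individual differences. An analyst who follows it as written fits a shared precision.

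A second reply concerns size, and it largely stands. A reader might infer that every variability test has a false-positive rate far above 5%. The documents do not support that, because they give no between-person spread, and without spread the rate is nominal. For Aim 2, stable differences add little, and the larger figures need a second assumption about person-specific shifts between phases.

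Third, the simulations are simpler than the protocol's model. They omit autocorrelation and, apart from the thinned runs, zeros. They also ignore the restriction "We will only include data for the CB-Abst group with confirmed abstinence" in phases 2 and 3, so 77 per arm is an upper figure for CB-Abst under the 77% completion assumption. For items with many zeros, such as suicidal or self-injury urges, fewer scores inform the precision and the inflation is smaller.

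Finally, it would be wrong to say that participants in the same arm and phase share one variance. In a beta regression they share a precision, and the variance still moves with the fitted mean.

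**Conclusion.** The concern holds in conditional form. As written, the variability tests are too liberal if adolescents differ in lability. H1.2 is the clearest case: about 9-24% at nominal 5% for an assumed log-precision SD of 0.3-0.5 with stable differences only, and lower for measures with many zeros. Aim 2 contrasts are about 6-11% at SD 0.5 with stable differences (12% in one 300-run repeat, within its error). They reach about 20-35% only if lability also shifts differently between phases, with assumed SD 0.2-0.3.

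It might also be inferred that the mean effects or Table 1 are compromised. They are not: the simulations take participant means as known and isolate the precision term, and Table 1 reproduces. This should be settled before analysis, but it is not a flaw in the design.

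**What to change.** In the Statistical models paragraph, add a participant-varying intercept to the residual-variance (precision) term, with a participant-varying use effect for H1.2 and participant-varying phase effects for Aim 2. An intercept alone is not enough. If the SAP already contains these terms, bring the protocol into line with it.

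State a fallback in case this does not converge for a sparse measure: participant-clustered inference (robust or participant bootstrap) for the dispersion contrasts, in H1.2 as well as Aim 2. For H1.2 the full model is preferable, because clustering corrected only partly in one of the two set-ups.

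Any summary-measure fallback should use non-zero scores and one value per participant and condition: use versus non-use prompts for H1.2, phase for Aim 2. One value per participant and phase cannot test H1.2, which is a contrast within phase 1. A log within-person SD that includes zeros is undefined for anyone who answers 0 throughout.

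The cost is a few sentences, longer model fitting and wider intervals for the variability effects. No new data are needed.

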**MetricWire (iOS & Android OS):** (<https://metricwire.com/>): EMA data capture will occur through Metricwire**,** a secure smartphone-based application with full-cycle project capabilities, including and most importantly for the current project is in-the-moment observation and reporting. This application is easily customizable to build sophisticated protocols using a simple drag-and-drop interface to engage participants under virtually any scenario and capture contextually relevant data. The application can be programmed with more the 60 different types of question formats, has both mobile and web participant-facing applications, and has functionality to notify participants of surveys to-be-completed via push notifications, SMS, voice, and email. Compliance management workflows deliver actionable information to ensure participant safety, maximize response rates and keep the study team on the same page. Relevant to this high-risk cohort, individualized safety plans can be pre-programmed into the application and can be delivered electronically to participants if safety concerns are reported during any EMA prompt type. Metricwire is currently the only EMA platform available that complies with HIPAA, FDA 21 part 11 and GDPR. All data collected will be stored with a unique random ID, making identification from survey responses impossible.

Aim 1: Primary outcomes will be depression items (e.g., bored, sad, tired, irritable) and SI intensity items (presence, urge, controllability) which are measured on a scale of “1 – Not at all” to “100 – Very Much” after each EMA prompt during the phase 1 of EMA.

Aim 2: Primary outcomes will be depression items (e.g., bored, sad, tired, irritable) and SI intensity items (presence, urge, controllability) which are measured on a scale of “1 – Not at all” to “100 – Very Much” after each EMA prompt during phases 1, 2 and 3 of EMA.

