**Potential Benefits to Society**

Information developed from this study may help researchers in the future. The expected scientific yield of the project is substantial. There is much to be learned from the project. Findings have the potential to have measurable implications on policy, prevention, and treatment efforts. The greatest benefit will be to future cohorts of adolescents who will benefit from what is learned from this research project.

The risks associated with this study are minimal and reasonable, particularly in light of the fact that significant knowledge will be gained.

1. **Statistical Analysis**

**Data preparation.** Six negative affect measures will be defined via composite averages and individual scores using EMA items: 1) the average over 5 items assessing depleted mood (scores for feeling Sad, Self-hatred, Numb, Hopeless, and Fatigued), 2) the average over 2 items assessing negative cognitive impacts (scores for feeling Disinterested and Inattentive), 3) the average over 3 items assessing negative activation (scores for feeling Agitated, Irritated, and Anxious), 4) the average over 3 items assessing passive suicidal ideation (scores for Thoughts about death, Wishing suffering could be over, and Better off as dead), 5) the individual item for suicidal urges, and 6) the individual item for non-suicidal self-injury urges. All items will be measured on a 0 (No, not at all) – 100 (Yes, very much) scale. Acute cannabis use will be defined as a binary indicator variable (1 = self-reported use in the hour preceding the current random prompt, 0 = no use in the last hour).Additionally, whether cannabis was used in the last hour to improve negative mood will be assessed on a 0 (No cannabis use) and 1 (No, not at all) – 100 (Yes, very much) scale.

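### The primary EMA outcomes are defined on two different scales, one of which has no zero, and the zero part of the model is named for H1.1 but not for H1.2 or Aim 2.

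*Protocol*

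**What the plan says.** **Outcome and scale.** The MetricWire paragraph of the Protocol (Platforms for Data Collection) states for both aims: "Primary outcomes will be depression items (e.g., bored, sad, tired, irritable) and SI intensity items (presence, urge, controllability". These items are scored from 1, labelled not at all, to 100. The Data preparation paragraph of Statistical Analysis instead defines six measures (four composites and two single items) and states: "All items will be measured on a 0 (No, not at all) – 100 (Yes, very much) scale". Bored and controllability, named in the first place, appear in none of the six measures.

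**Model.** The Statistical models paragraph assumes that "data are a mixture of a non-zero continuous component and zeros", with the non-zero part following a beta distribution. By default the zero part has "a participant-varying probability term governing the occurrence of zeros (to allow for individual differences"). The general rule is: "To test specific hypotheses, additional predictors will be included as needed for a) the beta regression", followed by two further places, the beta residual variance and the probability of a zero.

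**Placement by hypothesis (Data analysis).** For H1.1 the affect measures are "included as predictors for both the zero and non-zero components of the model". For H1.2, "the binary use indicator will be included as a predictor for the beta regression residual variance term as well". For Aim 2, after the group, phase and group-by-phase terms are listed, "All terms will be included as predictors for the beta regression residual variance term as well". The hypotheses speak of lower or higher mean scores without saying whether zeros are included.

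**The concern.** A two-part model needs a true zero, and it answers different questions in its two parts. One of the protocol's two scale definitions has no zero. For the hypotheses on relief after use (H1.2) and on change with abstinence (H2.1, H2.2), the Data analysis section does not carry the use, group or phase terms into the part that governs whether a score is zero.

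This matters most for the suicidal and self-injury outcomes, which make up three of the six measures (passive ideation, suicidal urges, self-injury urges). Entry requires a PHQ-9 score of at least 5 and sets no ideation criterion, so many zero answers are plausible. For such measures, moving from some ideation to none may be the main effect of interest. A comparison restricted to non-zero answers is also a comparison within a set that use or abstinence may itself have changed.

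**Working it through.** The protocol states no figure on this point, so there is none to reproduce. The check sets the passages side by side and then works out the consequence under stated assumptions.

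**1. Scale and items.**

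| | MetricWire paragraph | Data preparation paragraph |
|---|---|---|
| Lowest value | 1 (not at all) | 0 (not at all) |
| Raw zeros possible | No | Yes |
| Bored, controllability | Listed | In none of the six measures |

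The model rescales scores to lie between 0 and 1, but no rule says how the lowest recorded value maps to zero. The step from 0 to 1 is not trivial here. For the motive item in the same Data preparation paragraph, 0 means no cannabis use and 1 means not at all.

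**2. Placement of terms.**

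| | Beta mean | Beta residual variance | Zero probability |
|---|---|---|---|
| General rule | Permitted | Permitted | Permitted |
| H1.1 | Named | Not named | Named |
| H1.2 | Implied by the words as well | Named | Not named |
| Aim 2 | Implied by the words as well | Named | Not named |

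**3. Consequence if the terms stay in the beta part.** The identity is

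overall mean = P(non-zero) × mean of non-zero scores.

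Assumptions, none of them from the protocol: 40% of prompts non-zero; non-zero scores Beta(1.5, 3.5), mean 1.5/(1.5 + 3.5) = 0.30. The starting overall mean is 0.40 × 0.30 = 0.120. Suppose the lowest fraction f of the non-zero scores becomes zero:

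| f | P(non-zero) = 0.40 × (1 − f) | Non-zero mean | Overall mean | Change in overall mean |
|---|---|---|---|---|
| 10% | 0.36 | 0.328 | 0.118 | −1.5% |
| 20% | 0.32 | 0.357 | 0.114 | −4.8% |
| 30% | 0.28 | 0.386 | 0.108 | −9.8% |
| 50% | 0.20 | 0.452 | 0.090 | −25% |

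The non-zero mean rises while the overall mean falls. The relative change, (1 − f) × new non-zero mean / 0.30 − 1, does not involve the 40%, so the reversal does not hinge on that figure. The size of the absolute change does.

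If instead a random half of the non-zero scores becomes zero, the non-zero mean stays at 0.30 and the overall mean falls to 0.20 × 0.30 = 0.060. The beta part then shows nothing.

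**4. Simulation.** Assumptions: 77 participants per arm (half of the 154 in Table 1); 85 prompts in phase 1 and 42 in phase 3; 50% zeros; non-zero mean 30 out of 100; beta precision 4; participant variation in both parts; 600 runs. The test was a t-test on person-level change between arms, a simple stand-in for the planned model.

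| Change in CB-Abst only | Non-zero mean | Zero share | Overall mean |
|---|---|---|---|
| None | rejects 4.7% | 5.3% | 5.3% |
| Random scores to zero | +0.1 points, rejects 4.8% | +10.3 points, 100% | −3.15 points, 100% |
| Scores below 10 to zero | +5.9 points, rejects 100% | +10.6 points, 100% | −0.5 points, 11.3% |

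In the last row the non-zero part points the wrong way in every run. The overall mean has the right sign but little power, because the scores lost were small. That is why both parts need to be reported, and not the overall mean alone.

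**The case against.** The strongest reply is that the plan does not confine these effects to the non-zero part. The Statistical models paragraph lists the zero probability as one of three places for hypothesis predictors, and nothing in Data analysis withdraws it. The H1.2 and Aim 2 sentences do not name the beta mean either, so the words as well must refer back to something, and for H1.2 the nearest antecedent is the H1.1 sentence that names both parts. H1.1 also has a different outcome, motivated use, and its first prediction concerns the zero part, so that part had to be named there. This stands against the stronger reading that a reader might infer, namely that the plan excludes zeros from H1.2 and Aim 2 or that its test would report worsening. The text leaves the zero part unnamed; it does not exclude it.

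It can also be said that placement of terms belongs in the statistical analysis plan. That has some force, but the protocol does specify placement by hypothesis, and its specification is uneven.

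On size, the protocol gives no share of zeros. Four of the six measures are averages of two to five items and are zero only if every item is zero. Apparent worsening needs the lowest scores to be the ones that vanish; random loss gives no signal. These limits stand.

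None of this touches the conflict over scale and items, which is a contradiction within one document.

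**Conclusion.** The point holds in this form. The protocol contradicts itself on the scale and items of its primary EMA outcomes, and the model depends on which scale is in use: with raw scores of 1 to 100 and no recoding, its zero part has no data. Separately, Data analysis names the zero part for H1.1 but not for H1.2 or Aim 2, although the general rule would allow it, and leaves the target mean undefined.

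If the terms do stay in the beta part, ideation falling to zero would be missed or, where the lowest scores are the ones that go, could appear as a higher mean: non-zero mean 0.30 to between 0.33 and 0.45, against a fall of 1.5% to 25% in the overall mean. H2.1 is exposed in mirror image, since zeros turning into low scores would pull the non-zero mean down. These sizes rest on an assumed distribution and are illustrations, not predictions for this trial.

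**What to change.** 1. State that the use indicator (H1.2) and the group, phase and group-by-phase terms (Aim 2) enter the zero-probability part as well as the beta mean and residual variance.
2. State that the tests of lower or higher mean use the model-implied overall mean, P(non-zero) × non-zero mean, and report both parts beside it.
3. Check the minimum value that the app records. Then reconcile the MetricWire and Data preparation paragraphs on scale and items, and state how that minimum maps to zero.

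The cost is a wording change, one more set of coefficients per model, and one check of the app's settings. No added data collection is needed.
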